### Adverse events

2.10

AEs (serious and nonserious AEs), adverse drug reaction (ADR), and unexpected ADR will be defined accordingly to “ICH Guidance for Clinical Safety Data Management: Definitions and Standards for Expedited Reporting.”

All AE occurring between the first study-related procedure and the last study-related procedure will be reported. Those meeting the definition of serious AE (SAE) will be reported in an ad hoc SAE Form; they will be reported to coordinating center within 24 hours.

The following AEs have been reported during the use of Rapamycin, mainly in transplanted patients and in association with other drugs (Table 3).

**Table 3 T3:**
[figure not shown]
Adverse reactions reported with Rapamycin use.

Investigators must adhere to specific safety rules established for the following toxicities, regardless of the causal relationship to study treatment: respiratory toxicity; metabolic toxicity; cardiovascular toxicity; gastrointestinal toxicity; hematological toxicity; genitourinary toxicity; renal toxicity; reproductive system and pregnancy; hypersensitivity Reactions; skin toxicity; carcinogenicity; and increased susceptibility to infection.

The risk management plan for AEs not described above and suspected to be related to study treatment is as follows:

At the first occurrence of moderate AE (grade 2): study treatment will be interrupted until AEs has returned to baseline value or mild intensity, then resumed at the same dose level according to local investigator judgment.If the same moderate AE reoccurs, study treatment will be interrupted.In case of severe AE (grade 3), study treatment will be interrupted until AE has returned to baseline level or mild intensity, then resumed with a dose reduction (1 step).In case of life-threatening or disabling AE (grade 4), study treatment must be definitely discontinued.

### Safety assessment

2.11

Safety will be assessed on the following variables: occurrence of AEs and per-treatment arising changes in physical examination, vital signs (blood pressure, pulse rate, and body temperature), body weight, and clinical laboratory tests (biochemistry, hematology). MedDRA dictionary is going to be used for reporting.

All AEs will be actively collected at each visit, from spontaneous declarations of the patient as well as from oral inquiry and clinical examination. All concomitant medications and/or therapies should be documented in the patient file and reported in the electronic Case Report Form (eCRF).

The following biological parameters will be assessed according to study flow chart (Table 2)—hematology: count of red blood cells, hemoglobin, hematocrit, total white blood cells count, platelet count, and a differential count including neutrophils, lymphocytes, monocytes, eosinophils, and basophils; biochemistry includes urea, creatinine, albumin, protein electrophoresis, AST (SGOT), ALT (SGPT), gamma GT, LDH, cholesterol, triglycerides, sodium, potassium, glucose; screening for infectious diseases including HIV, hepatitis B, hepatitis C, and tuberculosis. An electrocardiogram and chest X-ray (only posterior–anterior view) will be performed at screening. At treatment end (week 18) these exams can be repeated based on clinical opinion of the caring neurologist.

A physical examination including vital signs (systolic and diastolic arterial pressure, heart rate) and body weight will be performed according to the Visit Schedule (Table 2). Check for adequate contraception will be performed at every visit. Respiratory function will be monitored with FVC.

Stopping rules for single patient have been established for each AE.

Stopping rule for the RCT has been established too. We will consider the following list of toxicities as acceptable: peripheral edema, hypertriglyceridemia, hypercholesterolemia, constipation, arthralgia, thrombocytopenia (not severe), anemia (not severe), leukopenia (not severe), rash, hypertension, increased creatinine, abdominal pain, diarrhoea, headache, fever, urinary tract infection, nausea, lymphocele, tachycardia, stomatitis, abnormal healing, increased lactic dehydrogenase, hypokalemia (not severe), diabetes mellitus, epistaxis, ovarian cysts, and menstrual disorders (amenorrhea and menorrhagia).

The study will be stopped by the DSMB in case of >30% of patients experience one of the following side effects: pneumonia, sepsis, venous thromboembolism, thrombotic thrombocytopenic purpura/hemolytic uremic syndrome, severe leukopenia or anemia or thrombocytopenia, bone necrosis, melanoma, and skin cancer. In other words, the trial will be stopped if any of the abovementioned SAEs occurs in ≥6 patients.

As for mild and moderate AEs, the DSMB will be notified if 50% of all subjects report a given mild or moderate severity adverse effect.

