### Randomization

2.4

Eligible patients will be randomized strictly sequentially, according to a randomization list prepared by the Biostatistician of the University of Modena.

All patients will receive a unique patient identification number at screening visit when signing the informed consent and before any study procedures are performed. Sixty-three patients will be randomized in the following 3 groups:

1.21 patients will receive Rapamycin 2 mg/m^2^/d + riluzole.2.21 patients will receive Rapamycin 1 mg/m^2^/d + riluzole3.21 patients will receive placebo + riluzole

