### Treatment and blindness

2.7

This study is a phase II randomized, double-blind, placebo-controlled, multicenter, clinical trial (RCT) to test Rapamycin in ALS patients. The study will include 63 ALS patients (EL Escorial Revised Criteria, sporadic and familial) with 1:1:1 allocation in 3 groups of 21 subjects each; treatment will be double blinded, and will last 18 weeks. Active treatment will include oral Rapamycin at 1 mg/m^2^/d or 2 mg/m^2^/d.

Rapamycin levels will be regularly measured and revealed only to an independent monitor, who will input Rapamycin levels on a separate eCRF, and on the basis of that value dosing changes may be performed at each treatment dispensation directly through eCRF (and blinded to caring neurologists who will supply bottles identified by a number and corresponding to different blinded doses) to keep Rapamycin levels from 4 to 12 ng/mL. Computerized randomization will be stratified by ΔFS (</≥0.7).

After treatment end (week 18) patients will be followed up for further 36 weeks. This large period of follow-up has the aim to assess potential late side effects of the treatment and to assess whether eventual biological or clinical effects of the treatment with respect to placebo, may last after drug discontinuation.

For the first 10 patients enrolled, clinical and biological safety assessments will be performed every week for the first month, and then every 2 weeks until the end of treatment. For the remaining 53 patients clinical assessments will be performed every 2 weeks for the first month, and then every 4 weeks during treatment duration.

If at either the interim or the final analyses safety concerns will arise, the trial will be stopped and all available data will be reviewed by the Study Steering Committee.

Table 2 shows study procedures to be undertaken.

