### Data recording and data monitoring

2.12

The investigators will collect data by entering them directly into the trial database, through electronic case report forms ad hoc developed. At the end of the RCT, database will be locked and an expert Statistician will check the database and extract all data for statistical analyses.

The study will be monitored by a certified contract research organization (CRO). A monitor will be in charge of safety data downloads and review on monthly basis (AEs), laboratory data downloads, including Rapamycin levels on fortnightly basis. Data safety and monitoring board (DSMB) meetings will be scheduled (starting when the first 10 patients enrolled would have been treated for 3 months and then when 50% of patients would have completed at least week 8 of treatment and subsequently after every 3 months). All SAEs will be reviewed by the DSMB. As for mild and moderate AEs, the DSMB will be notified if 50% of all subjects report a given mild or moderate severity adverse effect.

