### Sample size calculation

2.13

The sample size has been estimated considering as the primary outcome measure the proportion of positive response (Tregs number increase) at treatment end (18 weeks) in patients treated with Rapamycin versus placebo.

ALS patients have a slight reduction of Treg% (mean±SD: 2.1 ± 0.7) with respect to healthy controls (2.6 ± 0.6) (Treg% calculated on total lymphocytes; normal values of total lymphocytes: 1000–4500/μL; normal values of total Treg: 71.5 ± 17/μL).^[22]^

Slowly progressive ALS patients have a number of Tregs that is equal to healthy controls, whereas fast progressors have 31% fewer Tregs than slowly progressing patients, and Treg % is inversely correlated with the rate of disease progression.^[8]^ These data indicate that ALS patients have 60 ± 17 Treg/μL (fast progressors: 49.3 Treg/μL; slow progressors: 71.5 Treg/μL). As a result, a “positive response” can be considered an increase of the proportion of Tregs by ≥30%. The null hypothesis is that Rapamycin does not increase significantly the proportion of positive responses in treated patients at 18 weeks compared with their baseline stage and to placebo group. The alternative hypothesis is that Rapamycin determines a proportion of positive responses in ≥50% of treated patients compared with a maximum 5% of patients in the placebo group. The study has been designed to reject the null hypothesis with an alpha error of 0.025 (to take into account a multiple comparison with a control arm) and a power of 0.80. For this purpose, a sample of 54 patients randomized in 3 treatment arms would be needed. Considering an average drop out of 15% then a recruitment of 63 patients will be necessary.

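### The trial-stopping rule equates more than 30% of patients with 6 or more patients, but the two differ for every randomised group (7 of 21, 13 of 42, 19 of 63)

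*Protocol article*

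**What the plan says.** The Safety assessment section (2.11) gives the rule for stopping the whole trial in two consecutive sentences. The first is a percentage: "The study will be stopped by the DSMB in case of >30% of patients experience one of the following side effects", followed by a list that includes pneumonia, sepsis, venous thromboembolism and severe cytopenias. The second is a count, offered as a restatement: "In other words, the trial will be stopped if any of the abovementioned SAEs occurs in ≥6 patients". Neither sentence says whether the patients meant are those of one arm, of both rapamycin arms or of the whole trial. Neither says whether they are the patients planned or those treated so far.

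The group sizes stand elsewhere. Randomization (2.4): "Sixty-three patients will be randomized in the following 3 groups". Treatment and blindness (2.7): "with 1:1:1 allocation in 3 groups of 21 subjects each". Sample size calculation (2.13), before the 15% drop-out allowance: "a sample of 54 patients randomized in 3 treatment arms would be needed". Data recording and data monitoring (2.12) schedules the DSMB meetings, "starting when the first 10 patients enrolled would have been treated for 3 months".

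**The concern.** The second sentence claims to say the same as the first. If it does not, the DSMB holds a mandatory rule with two thresholds, and some event counts require a stop under one sentence and not under the other. The time to settle which applies is before events occur. Afterwards, the choice would be made knowing the data, and either decision could be disputed. The issue is not missing detail that a DSMB charter might supply: both thresholds are stated, and they are stated to be equal.

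**Working it through.** **Inputs.** Threshold above 30%, and threshold of 6 or more (2.11). Groups: 21 per arm and 63 in total (2.4, 2.7), hence 2 × 21 = 42 on rapamycin. Size before drop-out: 54 / 3 = 18 per arm (2.13). First DSMB meeting triggered by the first 10 patients (2.12).

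**Can the figure of 6 be reproduced?** The smallest count strictly above 30% of n is floor(0.3n) + 1.

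| Group | n | Smallest count above 30% | 6 as a share of n |
|---|---|---|---|
| First 10 patients | 10 | 4 | 60.0% |
| Arm before drop-out allowance | 18 | 6 | 33.3% |
| One arm as randomised | 21 | 7 | 28.6% |
| Both rapamycin arms | 42 | 13 | 14.3% |
| Whole trial | 63 | 19 | 9.5% |

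The formula gives 6 only for n = 17, 18 or 19. It gives 5 at n = 16 and 7 at n = 20. So 6 is reproduced from 18 per arm (5/18 = 27.8%, 6/18 = 33.3%) but from no randomised group. Reading the threshold as 30% or more still gives 7, 13 and 19 for the randomised groups.

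**Where the two sentences conflict at full enrolment.**
- One arm: at exactly 6 of 21, a gap of 7 − 6 = 1 patient.
- Both rapamycin arms: at 6 to 12 of 42, a gap of 13 − 6 = 7 patients.
- Whole trial: at 6 to 18 of 63, a gap of 19 − 6 = 13 patients.

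In each case the count is the stricter form. With 16 patients or fewer the percentage is stricter. If it were taken over the first 10 patients alone, 4 or 5 affected would meet the percentage but not the count.

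**How often it would matter.** The document gives no event rate, so true incidences of 5%, 10% and 20% are assumed. The chance of reaching each threshold is a binomial upper tail, P(X ≥ k) with X ~ Bin(n, p).

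| n | Threshold k | p = 5% | p = 10% | p = 20% |
|---|---|---|---|---|
| 21 | 6 (count) | 0.04% | 1.4% | 23% |
| 21 | 7 (above 30%) | 0.005% | 0.3% | 11% |
| 42 | 6 (count) | 1.7% | 24% | 87% |
| 42 | 13 (above 30%) | <0.001% | 0.02% | 6.2% |
| 63 | 6 (count) | 9% | 61% | 99% |
| 63 | 19 (above 30%) | <0.001% | <0.001% | 3.6% |
| 10 | 4 (above 30%) | 0.1% | 1.3% | 12% |
| 10 | 6 (count) | 0.0003% | 0.015% | 0.6% |

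**The case against.** The strongest reply is that the rule was meant per arm and worked out on 18 evaluable patients, where 6 is exactly the first count above 30%. The error is then only a failure to update for the drop-out allowance: 6 against 7 of 21, or 1.4% against 0.3% at a 10% incidence. The neighbouring notification rule for mild and moderate events refers expressly to all subjects, while the stopping rule does not, which gives some support against the whole-trial reading. The count is also explicit, and a DSMB that applies it at full enrolment stops no later than the percentage requires.

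The early-look case is also open to challenge. Enrolment is not said to pause after 10 patients. If 63 patients enrol steadily over the 12 months in section 2.15 (5.25 a month), 10 + 3 × 5.25 = 25.75, so about 25 are enrolled when the first meeting falls due. More than 30% of 25 is 8, and the count is still the stricter form. At half that speed, 10 + 3 × 2.625 = 17.9, so about 17, where the two forms agree. Moreover, the DSMB reviews every SAE (2.12), and section 2.7 allows a stop for safety concerns in general.

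Most of this stands as a limit on size. The per-arm origin is plausible, no protection is lost at full enrolment if the count is used, and the reversal at 10 patients arises only if the percentage is taken over those 10 or recruitment is much slower than assumed. It does not reconcile the sentences. The rule mentions neither an arm nor 18 nor evaluable patients. The safety analysis in 2.14 covers everyone who receives at least one dose, so up to 21 per arm. General DSMB review does not say which threshold is binding.

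**Conclusion.** The concern holds. The two forms of the stopping rule are not equivalent for any randomised group, and a mandatory rule should have only one reading. The size depends on the denominator, which the text does not give: one patient per arm, 7 on pooled rapamycin, 13 in the whole trial. On the per-arm reading the practical effect is small. On the whole-trial reading, an assumed 10% incidence would trigger the count 61% of the time and the percentage almost never. At full enrolment the likely harm is a dispute, or a stop that the percentage does not require, rather than lost protection.

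The counts follow exactly from the document. The probabilities illustrate only: they rest on assumed incidences and independent patients, and apply to whatever event definition, single or combined, has that incidence. This should be corrected, but it does not threaten the design.

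**What to change.** Amend section 2.11 to state one governing threshold with its denominator, and correct the other form to match. Two examples: at least 6 patients in a rapamycin arm of 21 (28.6%); or more than 30%, that is at least 7 of 21. Say whether the fixed count or the percentage of patients treated so far applies at interim DSMB meetings, since more than 30% of 10 patients is 4. State also whether the listed events are counted singly or together. The choice of threshold belongs to the DSMB. The cost is a wording amendment, with no extra patients and no new data.

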### Role of participating centers

2.15

Our study group includes 8 centers (Turin, Modena, Genoa, Padua, Novara, and 3 centers in Milan) that have a longstanding history on ALS management, and are referral centers for ALS care following >150 patients/y each. They share an established collaboration in the field of ALS, in clinical management of patients, in the realization of clinical trials, genetic, and epidemiological studies. The analysis of biomarkers will be centralized and performed in a renowned laboratory (University of Modena and Reggio Emilia), with large experience in cell analysis and is internationally renowned for the use of flow cytometry for studies on several human diseases. Randomization and statistics will be also centralized to orchestrate the different phases of the project. Statistical Unit of the University of Modena and Reggio Emilia has considerable experience on RCT project and management, and on data analysis. All trial activities will be monitored by a CRO.

Each center is expected

1.to randomize ≥7 patients fulfilling including and excluding criteria in a period of 12 months and to administer the treatment for 18 weeks;2.to provide 1 principal investigator and 1 neurologist to evaluate including and excluding criteria, get an informed consent, administer treatment, and assess primary and secondary outcome;3.to provide a person who will send Rapamycin dosage to the coordinating center and who will not see patients; and4.to formally adhere to the practice parameters of the European Federation of Neurological Societies concerning the standardization of the management of the patient in terms of ventilatory support and nutrition.

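### The only numerical trial stopping rule is given in two forms that do not agree, more than 30% of patients and six or more patients, with no denominator named

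*Protocol article*

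**What the plan says.** Section 2.11 (Safety assessment) gives the rule first as a percentage: "The study will be stopped by the DSMB in case of >30% of patients experience one of the following side effects". The list that follows includes pneumonia, sepsis, venous thromboembolism, severe cytopenias and skin cancer. The next sentence turns the percentage into a count: "In other words, the trial will be stopped if any of the abovementioned SAEs occurs in ≥6 patients". Neither sentence says whether the patients are those of the whole trial, of the rapamycin arms together, or of one arm.

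The companion rule for milder events does name its base: "the DSMB will be notified if 50% of all subjects report a given mild or moderate severity adverse effect".

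Section 2.4 fixes the trial size: "Sixty-three patients will be randomized in the following 3 groups", with 21 in each. Section 2.13 gives the size before allowance for dropout: "a sample of 54 patients randomized in 3 treatment arms would be needed", which is 18 per arm. Section 2.14 bases the safety analysis on everyone who takes at least one dose.

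**The concern.** A percentage and a count joined as restatements of each other should describe the same event. Here they do so only for a group size that the rule does not name. The DSMB would therefore have to settle what the rule means during the trial, with accumulating data in view.

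The main practical question is whether six patients are counted across the trial or within an arm. Counted across the trial, the rule ignores allocation: six placebo patients with a listed event and none on rapamycin would end the study. Counted within an arm, it is a much less sensitive trigger, and count and percentage still disagree at 21 patients.

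A second ambiguity compounds this. The percentage sentence can be read as any listed event combined, and the count sentence as each event type separately. The choice changes how soon six is reached.

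**Working it through.** **Inputs.** 63 randomised, 21 per arm, so 42 on rapamycin (sections 2.4 and 2.7). 54 before dropout, so 54/3 = 18 per arm (section 2.13). Thresholds of more than 30% and of six or more (section 2.11).

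**Step 1: try to reproduce the stated equivalence.** The smallest count k with k/n > 0.30, next to six as a share of n:

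| Group | n | 0.30 × n | Smallest count above 30% | 6/n |
|---|---|---|---|---|
| All randomised | 63 | 18.9 | 19 | 9.5% |
| Both rapamycin arms | 42 | 12.6 | 13 | 14.3% |
| One arm as randomised | 21 | 6.3 | 7 | 28.6% |
| One arm before dropout inflation | 18 | 5.4 | 6 | 33.3% |

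For n = 16 the smallest count is 5; for n = 17, 18 and 19 it is 6; for n = 20 it is 7. Six therefore reproduces only for 17 to 19 patients. The one such number derivable from the protocol is 18 per arm.

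**Step 2: what an inert drug would do.** The protocol gives no event rate, so I assume that each patient, in every arm, has a risk p of 5%, 10% or 15% of a counted event over the whole study. The figures are exact binomial. For the whole trial the probability is P(X ≥ 6), X ~ Bin(63, p). For a rule applied to each rapamycin arm it is 1 − (1 − P(X ≥ k))², X ~ Bin(21, p).

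| Rule | p = 5% | p = 10% | p = 15% |
|---|---|---|---|
| ≥6 of 63 | 9% | 61% | 93% |
| ≥6 of 21 in either rapamycin arm | 0.1% | 3% | 16% |
| ≥7 of 21 in either rapamycin arm | 0.01% | 0.7% | 6% |

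Example at p = 10%: P(X ≥ 6 | 21) = 0.0144, so 1 − (1 − 0.0144)² = 0.029.

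**Step 3: what a true excess would do.** Placebo risk is p, and both rapamycin arms have p plus 20 points. The whole-trial total is the convolution of the arms' binomials; the per-arm rules use the formula in step 2 with the raised risk.

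| Rule | p = 5% | p = 10% | p = 15% |
|---|---|---|---|
| ≥6 of 63 | 98.5% | 99.9% | >99.9% |
| ≥6 of 21 in either rapamycin arm | 68% | 87% | 96% |
| ≥7 of 21 in either rapamycin arm | 45% | 70% | 87% |

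For a 10-point excess the corresponding ranges are 76% to 99.7%, 16% to 68%, and 6% to 45%.

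The whole-trial count is sensitive largely because it fires on background events. The per-arm rule gives up sensitivity in exchange for specificity. One patient more or less per arm matters: at p = 5% with a 20-point excess, moving from 6 to 7 lowers the chance of a trigger from 68% to 45%.

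**The case against.** The best defence is that one arm was meant. On 18 evaluable patients per arm the two forms agree exactly, and on 21 they differ by a single patient. The count is also the concrete instruction, and a DSMB would probably follow it. This is a plausible account of where six came from, and it limits the gap if it is right. It does not repair the text: the rule mentions neither an arm nor 18, each arm randomises 21, and safety is assessed in everyone dosed, not in those left after dropout.

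Other protections exist. Section 2.12 states "All SAEs will be reviewed by the DSMB", and section 2.7 says the trial will be stopped if safety concerns arise at an interim or final analysis. A reader might infer that section 2.11 holds the only mandatory stop for the whole trial. It does not; it holds the only one with a number.

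A reader might also infer that up to 18 patients in one rapamycin arm could have a listed event without a stop, because 18 of 63 is 28.6%. The document does not support that: 18 exceeds the explicit count of six on any reading of the denominator, unless those events are counted by type and spread over several types. Nor is the switch from side effects to SAEs a separate fault, since the second sentence points back to the same list.

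Finally, the forced-stop probabilities rest on assumed risks. They show what the whole-trial reading would imply, not that a false stop is likely.

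**Conclusion.** The concern holds. The rule is wrong as written: its percentage and its count are presented as the same limit but differ for 63, 42 and 21 patients, and no denominator is given. That finding is arithmetic on the protocol's own numbers and needs no assumption.

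The size depends on the reading. Within an arm of 21 the discrepancy is one patient. If six is counted across the trial, the rule can be met by placebo cases alone, and an inert drug meets it with probability 9% to 93% over assumed risks of 5% to 15%. Those probabilities treat patients as independent, with full follow-up and one type of count. If each event type is counted separately, they apply to one type at its own risk.

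The document does not settle whether the percentage or the count should govern. The sponsor should correct the rule, but this does not undermine the trial's design as a whole.

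**What to change.** In section 2.11:

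- Name the denominator. Each rapamycin arm as randomised (n = 21) is the most sensible choice, because placebo cases alone could then not stop the trial.
- State one threshold whose count and percentage agree: at least 7 of 21 (33%, so above 30%) if the percentage governs, or at least 6 of 21 (29%) if the count governs. The sponsor and the DSMB should confirm which. This is a safety-policy choice that the statistics inform but do not decide.
- Say whether the count is for each listed event type or for any listed event combined.

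The change is one of wording and needs no new data or visits, though the DSMB will need its SAE listing split by coded arm. The cost is sensitivity compared with six cases across all arms. At the assumed background risks, a 20-point excess in both rapamycin arms triggers the rule 68% to 96% of the time with 6 of 21, or 45% to 87% with 7 of 21, against 98.5% to more than 99.9%. The DSMB's review of every SAE and the general provision in section 2.7 to stop on safety concerns remain as backstops.

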### Objectives

2.1

The primary objective is to assess whether different Rapamycin doses increase Treg number in ALS patients compared with the control arm.

Secondary objectives include the following:

1.*Assessment of Rapamycin safety and tolerability in a cohort of ALS patients*: occurrence of adverse events (AEs), changes on clinical examination including vital signs and weight, and laboratory examinations (biochemistry, hematology and urinalysis) will be registered throughout the entire study duration.2.*Biological assessment*: To analyze Rapamycin efficacy in inhibiting MTOR pathway, by quantifying the phosphorylation of the S6 ribosomal protein (S6RP) comparing baseline and weeks 8, 18 (treatment end), 30, and 54 between Rapamycin arms and placebo arm. To identify changes in activation and homing capabilities of different T, B, NK cell subpopulations comparing baseline and weeks 8, 18 (treatment end), 30, and 54 between Rapamycin arms and placebo arm. To study Rapamycin effects on different biomarkers (including peripheral and CSF biomarkers, that is, creatinine and albumin, CK, vitamin D, plasma/CSF neurofilament heavy/light chain protein) comparing baseline and week 8, 18 (treatment end), 30, and 54 between Rapamycin arms and placebo arm. To identify Rapamycin-induced changes in inflammatory status, by the molecular analysis of the inflammasome system baseline and week 8, 18 (treatment end), 30, and 54 between Rapamycin arms and placebo arm. To assess Rapamycin capacity to pass through blood–brain barrier (BBB).3.*Clinical assessment*: to assess changes in Amyotrophic Lateral Sclerosis Functional Rating Scale (ALSFRS)-Revised from baseline to weeks 4, 8, 12, 18, 30, 42, and 54 in placebo and treatment arms; overall survival from randomization to date of documented death or tracheostomy; survival rate at weeks 18, 30, 42, and 54; forced vital capacity (FVC) score from baseline to weeks 4, 8, 12, 18, 30, 42, and 54.4.Quality of life assessment: ALSAQ-40 from baseline to weeks 8, 18, 30, and 54 in treatment and placebo arms.

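### The DSMB notification for mild and moderate adverse events counts half of all three arms pooled, so it is insensitive to an effect of one dose or of the drug

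*Protocol article*

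**What the plan says.** Section 2.11 (Safety assessment) sets a notification rule for non-serious toxicity: "the DSMB will be notified if 50% of all subjects report a given mild or moderate severity adverse effect". Section 2.12 (Data recording and data monitoring) repeats it: "As for mild and moderate AEs, the DSMB will be notified if 50% of all subjects report a given mild or moderate severity adverse effect". Neither place gives a version by arm or by dose, and neither gives a counting window.

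The arms are fixed elsewhere. Section 2.4: "Sixty-three patients will be randomized in the following 3 groups". Section 2.7: "with 1:1:1 allocation in 3 groups of 21 subjects each", and "Active treatment will include oral Rapamycin at 1 mg/m^2^/d or 2 mg/m^2^/d". The third arm is placebo. The first secondary objective (2.1) is: "Assessment of Rapamycin safety and tolerability in a cohort of ALS patients".

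Directly before the notification rule, 2.11 gives a trial-level stopping rule in two forms: "The study will be stopped by the DSMB in case of >30% of patients experience one of the following side effects" and, as a restatement, "the trial will be stopped if any of the abovementioned SAEs occurs in ≥6 patients".

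Other safety review is described too. Under 2.12 a monitor reviews adverse events monthly. The DSMB reviews all serious events and meets after the first 10 patients have had 3 months of treatment, again when half the patients have completed week 8, and every 3 months after that. Section 2.14 plans a comparison of adverse events between arms.

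**The concern.** A trial with two doses and a placebo arm should be able to show a tolerability problem that belongs to the drug or to one dose. A rule that pools all arms dilutes that pattern: placebo patients, and patients on the other dose, enter the denominator whether or not they could have the effect. Each arm is one third of the trial and the threshold is one half, so no single arm can reach it alone.

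At stake is whether the one numerical trigger set for mild and moderate events does useful work for the first secondary objective. The primary analysis is not affected.

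**Working it through.** **Inputs.** 63 randomised, 21 per arm, 1:1:1 (2.4, 2.7); threshold 50% of all subjects (2.11, 2.12).

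**The plan's own sample size, which sets the arm size.** Section 2.13 uses 50% versus 5%, alpha 0.025 and power 0.80. The pooled-variance formula for two proportions, two-sided and without continuity correction, has mean proportion 0.275:

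- n = [2.241 × √(2 × 0.275 × 0.725) + 0.842 × √(0.5 × 0.5 + 0.05 × 0.95)]² / 0.45² = 17.4, so 18 per arm and 54 in all, as stated.
- 54 × 1.15 = 62.1, so 63 in three arms of 21. (54 / 0.85 gives 64, a difference of one patient that does not matter here.)

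**Threshold.** 0.5 × 63 = 31.5, so 32 patients.

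**One dose arm fully affected.** 21 / 63 = 33.3%, below 50%. Extra cases needed: 32 − 21 = 11 of the other 42, or 26.2%. If each of those 42 has the event independently at rate p, the chance of a notification is P(Binomial(42, p) ≥ 11):

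| Rate p in the other two arms (assumed) | Chance of notification |
|---|---|
| 0% | 0 |
| 10% | 0.2% |
| 15% | 4.2% |
| 20% | 20.5% |
| 25% | 48.8% |
| 30% | 75.6% |

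**Both doses affected.** With no placebo cases, 32 / 42 = 76.2% of rapamycin patients must report the event. With assumed rates, summing three independent binomials of 21:

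| Dose A / dose B / placebo | Expected total | Chance of ≥32 |
|---|---|---|
| 60% / 60% / 10% | 27.3 | 11% |
| 70% / 70% / 10% | 31.5 | 50% |
| 80% / 40% / 10% | 27.3 | 10% |
| 100% / 50% / 10% | 33.6 | 78% |

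**Other readings of the denominator.** On the 54 evaluable patients the threshold is 27 and one arm is 18 (33.3%). If the rule means those enrolled so far, one arm stays near one third under 1:1:1 allocation. Neither reading changes the result.

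**The same 50% within an arm.** 0.5 × 21 = 10.5, so 11 of 21. At a true rate of 60% in one arm, P(Binomial(21, 0.6) ≥ 11) = 83%. At an assumed 20% in all three arms, the chance per arm is 0.1%, and for any of the three it is 1 − (1 − 0.001)³ = 0.3% per event type. With few patients it is noisier: with 3 treated per arm the threshold is 2, P(Binomial(3, 0.2) ≥ 2) = 3 × 0.04 × 0.8 + 0.008 = 10.4%, and for any of three arms 1 − 0.896³ = 28%. A minimum number is therefore needed.

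**The neighbouring stopping rule.** More than 30% means 19 of 63 (18.9), 7 of 21 (6.3) or 6 of 18 (5.4). The stated count of 6 fits one arm of 18 and not the whole trial, while the next sentence in 2.11 counts all subjects.

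**The case against.** The strongest reply is that this is an added notification and not the route by which tolerability is judged. Monthly review, scheduled DSMB meetings, review of all serious events and the by-arm comparison in 2.14 do not depend on it. A reader might infer from the arithmetic that a one-dose toxicity would stay hidden from the DSMB. The documents do not support that; they are silent on whether mild and moderate events are tabulated by arm at the meetings, which an article may leave to a charter.

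A high threshold may also be deliberate. Section 2.11 lists toxicities accepted in advance, among them stomatitis, rash and peripheral oedema, and 2.2 says the protocol was revised on the DSMB's suggestions. Section 2.7 adjusts dosing toward one blood-level range in both dose arms, so exposures may converge and an effect wholly confined to one arm is an extreme case. A pooled count can also be run without unblinding anyone. All of this stands, and it limits the consequence. It does not make a pooled half a sensitive trigger: the case of both doses needs no confinement to one arm and still requires 76% when placebo has none.

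Two further inferences go too far. One is that the rule responds mainly to background disease: no background rate is given, and an evenly spread complaint must itself reach about half of all patients. The other is that follow-up events after treatment certainly count: 2.10 reports events up to the last study procedure, but the rule itself states no window.

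**Conclusion.** The concern holds as a limited design point. The rule as written cannot be triggered by one dose arm alone (21 of 63 against a threshold of 32). It needs 26% of the remaining patients as well, or 76% of rapamycin patients if placebo has none. Those figures rest only on the stated arm sizes and threshold. The notification probabilities rest on assumed event rates and independence between patients.

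The trigger therefore adds little for drug- or dose-related mild and moderate events. It does not follow that safety review as a whole fails. The two adjacent rules in 2.11 also appear to use different denominators. The documents do not settle which denominator the stopping rule intends, so the sponsor must state and reconcile it.

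**What to change.** In 2.11 and 2.12:

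- Keep the pooled notification, and add the sponsor's own 50% threshold within each randomised arm (11 of 21 at full enrolment), with the concurrent placebo count shown beside it.
- Apply the by-arm threshold only once a stated minimum number per arm has been treated, so that 2 of 3 patients does not trigger it.
- Show on-treatment and follow-up events separately. Do not drop the latter, because 2.7 gives late side effects as a reason for the 36-week follow-up.
- Have the by-arm table prepared for the DSMB by an unblinded party separate from the site teams and from the trial analysts. The statistical unit named in 2.15 also does the data analysis, so it is not the natural holder.
- State the denominator of each rule in 2.11, and reconcile the percentage and count forms of the stopping rule.

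The cost is a few sentences, one unblinded tabulation and some more notifications for benign events. A notification does not stop the trial, and the by-arm addition alters no stopping or treatment rule.
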